### 2.4. Assessment of Preclinical ILD

At baseline, subjects will be stratified into two groups based on the presence (ILD changes group) or absence (no ILD changes group) of ILD changes on HRCT scan (Figure 1). ILD changes are defined as extensive disease, familial interstitial lung abnormalities (FILA) or minimal FILA (see Box 1). The definition of FILA is based on the position paper of the Fleischner Society on interstitial lung abnormalities (ILA) [21]. The position paper does not consider abnormalities identified during screening for ILD in high-risk groups, including familial ILD, as ILAs because they are not incidental. The Society suggests the term preclinical ILD for such cases, however, this suggests that subjects have ILD which is not always the case. Therefore, we added familial (F) to refer to the context of the findings, which together makes FILA. To define all possible abnormalities during screening, minimal FILA will be defined as FILA in less than 5% of the lung zone (see Box 1).

A thoracic radiologist will assess the HRCT scan. All the findings of study visits will be discussed with an expert pulmonologist in the field and, when necessary, in a multidisciplinary discussion. If ILD changes or other abnormalities in clinical parameters are found that warrant evaluation, participants will remain in the study, but will also be referred to regular care for examination by a general practitioner or pulmonologist.

Box 1Definition of ILD changes in the FLORIS study.ILD changes on HRCT scan in first-degree family members of FPF patients are defined as:
Extensive disease: non-trivial abnormalities present in three or more lung zones (a)FILA: Any of the following non-dependent abnormalities involving >5% of a lung zone: traction bronchiectasis, honeycombing, ground-glass or reticular abnormal-ities, lung distortion and non-emphysematous cysts (a)Minimal FILA: Any of the following non-dependent abnormalities involving <5% of a lung zone: traction bronchiectasis, honeycombing, ground-glass or reticular abnormalities, lung distortion and non-emphysematous cysts
(a) Concepts are based on the definition of ILA by Hatabu et al. [21] for incidental findings and adjusted to a screening setting of high-risk relatives

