### 2.12. Sample Size

The sample size was calculated based on our own retrospective data and literature. In pilot screening, we detected ILD changes in 13 of 73 (18%) asymptomatic, at-risk relatives, while in the literature, ILD changes were seen in 16–23% of the HRCT-scans [15,18,19,57]. In the present study, we will include 200 participants, with an expected ratio of 37 participants with the presence of ILD changes and 163 participants with the absence of ILD changes at HRCT scan.

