### 2.13. Statistical Analysis

Categorical variables, including presence/absence of Velcro-like crackles, presence/absence of clubbing, MRC dyspnea scale, and *MUC5B* rs35705950 genotype will be expressed as numbers with percentages. Continuous variables, including FVC, TLC, DLCO (corrected for hemoglobin), VAS Cough score, MMP7 level, CCL18 level, KL-6 level, SP-D level, and 6MWT (distance in meters, sat O2 rest, sat O2 after 6MWT, sat O2 nadir, and sat O2 rest minus sat O2 nadir) will be displayed as means with standard deviations or medians with standard error, where appropriate.

The primary objective will be tested using a chi-square test or Fisher-exact test (as appropriate for categorical variables) and Student’s *t*-test or Mann–Whitney U test for continuous variables. Univariate logistic regression will be used to test which parameters differ between the groups. Parameters that are found to be diagnostic in univariate analysis with *p* < 0.20, will subsequently be assessed in a multivariate logistic regression analysis using the backward method to determine which are the strongest predictors for ILD changes on HRCT scan at baseline. In case too many parameters meet the *p* < 0.20 criterion, a cut-off of *p* < 0.10 will be used.

The secondary objective will be tested using the paired *t*-test, or Wilcoxon signed-rank test for the differences between the groups, and a repeated measure ANOVA test for the differences within the same group over time. After year 2, linear mixed models will be used to determine the strength of change of the parameters over time within and between both groups.

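### The plan names the equal-variance Student's t-test for baseline groups expected at 37 v 163, where its error rate depends on an unknown ratio of spreads; Welch's test would remove that dependence (minor)

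*Protocol article*

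**What the plan says.** Section 2.13 of the protocol article tests the primary objective with a chi-square or Fisher test for categorical parameters and, for continuous ones, Student's "t*-test or Mann–Whitney U test for continuous variables". It lists 13 continuous measures: FVC, TLC, DLCO, the cough score, four serum markers and five walk-test measures. It does not mention an unequal-variance version.

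The same section adds a second test of the same contrast: "Univariate logistic regression will be used to test which parameters differ between the groups". Parameters then enter a multivariate logistic model if p<0.20 in univariate analysis, or p<0.10 if too many qualify. No 5% level is stated.

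Section 2.12 gives the group sizes: 200 participants "with an expected ratio of 37 participants with the presence of ILD changes and 163 participants with the absence of ILD changes". Section 2.4 describes the smaller group: "ILD changes are defined as extensive disease, familial interstitial lung abnormalities (FILA) or minimal FILA". No SD is given for any parameter in either group.

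**The concern.** Student's t-test estimates one common SD from both groups. At 37 v 163, 162 of the 198 degrees of freedom come from the larger group, while most of the uncertainty in the mean difference comes from the smaller one. If the smaller group is more variable, the pooled standard error is too small and the test rejects too often. If it is less variable, the test rejects too rarely. With groups of equal size the two effects largely cancel; at about 1:4.4 they do not.

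The Discussion says that parameters found to predict HRCT changes may help decide who is scanned, and that those lacking predictive value may be dropped from clinical screening. A test that responds to spread as well as level can err in either direction for that purpose. The test is named in the text, so the point concerns a stated choice and not a detail left open.

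**Working it through.** **Group sizes.** The pilot figure is "we detected ILD changes in 13 of 73 (18%) asymptomatic, at-risk relatives", and 200 × 13/73 = 35.6. The literature range in Section 2.12, "ILD changes were seen in 16–23% of the HRCT-scans", gives 32 to 46 out of 200. The stated 37 is 37/200 = 18.5%, which is consistent with both. The remaining 163 give a ratio of 163/37 = 4.4.

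**Formula.** Let r be the SD in the ILD-changes group divided by the SD in the other group, the latter set to 1. Every value of r is an assumption.

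- True variance of the mean difference: V_true = r²/37 + 1/163
- Variance the pooled test uses, on average: V_pooled = [(36r² + 162)/198] × (1/37 + 1/163)
- Approximate rejection rate under equal means at two-sided 5%: 2 × [1 − Φ(1.972 × √(V_pooled/V_true))], where 1.972 is the 97.5% point of t on 198 df

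**r = 1.5.** V_true = 0.06081 + 0.00613 = 0.06695. V_pooled = (243/198) × 0.03316 = 0.04070. √(0.04070/0.06695) = 0.780, and 1.972 × 0.780 = 1.538. The rate is 12.4%.

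**r = 2.0.** V_true = 0.10811 + 0.00613 = 0.11424. V_pooled = (306/198) × 0.03316 = 0.05125. √(0.05125/0.11424) = 0.670, and 1.972 × 0.670 = 1.321. The rate is 18.7%.

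**Simulation.** Normal data, equal means, n = 37 and 163; 40,000 replicates for the t-tests and 20,000 for Mann–Whitney and univariate logistic regression (Wald). Cells are rejection percentages; a dash means not run.

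| r | Student, formula, 5% | Student, 5% | Welch, 5% | Mann–Whitney, 5% | Logistic, 5% | Student, p<0.20 | Logistic, p<0.20 |
|---|---|---|---|---|---|---|---|
| 0.67 | 1.2 | 1.3 | 5.1 | 2.3 | – | 10.2 | – |
| 1.0 | 4.9 | 5.1 | 5.0 | 5.1 | 4.9 | 19.8 | 20.1 |
| 1.25 | 8.7 | 8.8 | 5.1 | 6.9 | 9.0 | 26.5 | 27.1 |
| 1.5 | 12.4 | 12.8 | 5.2 | 8.7 | 11.9 | 31.7 | 31.3 |
| 2.0 | 18.7 | 18.9 | 5.1 | 11.2 | 18.8 | 39.3 | 39.3 |

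**Alternatives.** In a separate run of 6,000 replicates per ratio, Brunner–Munzel rejected 5.0% at r = 1.5 and 5.1% at r = 2.0. Robust (sandwich) standard errors in the univariate logistic model gave 6.5% and 7.2%, closer to nominal but not at it.

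**Price.** For a true difference of 0.5 SD with equal variances, power is 78.4% with Student and 77.3% with Welch, a loss of 1.1 percentage points.

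**The case against.** **The null may not apply.** The obvious reason for wider spread in the ILD-changes group is its mix of minimal FILA and extensive disease, but that mix would usually move the mean too. Suppose minimal cases resemble the no-changes group, a fraction p is shifted by d, and the SD within each subgroup is 1. Then r = 1.5 requires p(1−p)d² = 1.25, and the group mean shifts by pd: 0.37 SD at p = 10%, 0.73 at 30% and 1.12 at 50%. Rejecting there is correct detection. This stands: severity mixing on its own does not produce the equal-means scenario in the table.

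**The direction could be reversed.** Section 2.2 enrols from age 18, and the Discussion reports that relatives with interstitial abnormalities were older in previous studies. The no-changes group may therefore span more ages and vary more on age-dependent measures. All participants are asymptomatic without a previous ILD diagnosis, which limits severity in the other group. This stands against any claim of a known inflation. It does not favour Student's test, which would then be too conservative.

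**The remedy misses the screening step.** Section 2.13 ties selection to univariate analysis, most naturally read as the logistic regression, and Welch leaves that untouched. This stands and is stated as a limitation.

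**Some of this is detail for a full plan.** Variance handling is often settled there, and skewed measures may take the rank route, where the distortion is smaller. This lowers the importance but does not remove the point, because the article names the equal-variance test.

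**Conclusion.** The point holds as a conditional and minor one. The named t-test does not hold its level at 37 v 163 unless the spreads are equal. For SD ratios from 0.67 to 2.0 its rejection rate at a nominal 5% runs from about 1% to about 19%, and Welch's stays close to 5%. At the article's p<0.20 threshold a pooled t-test would reject about 32% at ratio 1.5 and 39% at 2.0. These figures assume normal data, equal means, the expected group sizes and SD ratios that the article does not supply.

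A reader might infer that the primary comparison has a false-positive rate of 12–19%. The article does not support that: it gives no SDs, sets no 5% level, and leaves open which group varies more. Nor can it be said that planned confidence intervals are too narrow, since Section 2.13 plans none for the mean difference.

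**What to change.** In Section 2.13, replace Student's t-test with Welch's unequal-variance t-test for the continuous baseline comparisons. Where a rank test is chosen, use Brunner–Munzel in place of Mann–Whitney; it tests whether values in one group tend to exceed those in the other without assuming equal spread. Decide this in advance and not after a preliminary test of variances.

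The cost is one sentence of wording and about 1 percentage point of power if the variances are equal. The change does not correct the univariate logistic regression. Robust standard errors could be added there, on the understanding that they repair it only in part.

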## 2. Materials and Methods

### 2.1. Objectives and Endpoints

The primary objective of the FLORIS study is to determine the diagnostic value of parameters for early disease detection in first-degree relatives of patients with FPF. To this end, the presence or absence of ILD changes on a baseline HRCT scan (see Figure 1) will be used to determine the predictive value for early disease of a set of clinical and exploratory parameters (see Table 1).

As secondary objectives, the study aims to gain insight into the natural history of FPF and to determine the necessary interval between screening visits. Secondary endpoints will assess the change in parameters between baseline and follow-up after one and two years within each group separately, and analyze differences between the groups with and without ILD-changes (see Figure 1).

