## 3. Discussion

The FLORIS study will be one of the first longitudinal cohort studies of this size to screen asymptomatic family members of FPF patients using an extensive screening protocol with tightly scheduled study visits. It will provide information for an evidence-based screening protocol for preclinical disease in at-risk relatives.

Description of study protocols in advance of obtaining study results is considered to add background information on the trial and reduce (publication) bias [58]. In the setting of FPF, the current study description may provide background for future screening protocols.

The primary aim of the current protocol is to determine the reliability of screening parameters to predict HRCT abnormalities. The HRCT scan has proven to be a valuable screening tool to detect interstitial changes in asymptomatic, at-risk relatives [15,17,18,19,20]. However, it is also expensive and not suitable for yearly use due to radiation exposure in healthy individuals. We hypothesize that in addition to currently used methods, a combination of patient-reported symptoms and physiological markers can serve as early predictors for the development of FPF. There will be an emphasis on easy-to-use, minimally invasive markers to investigate whether (a subset of) the screening activities could be transferred to the general practice in the future. Ideally, FLORIS will enable us to identify parameters that can accurately predict the presence of ILD changes on an HRCT scan, thereby making it possible to select who should undergo an HRCT scan and for whom this is not (yet) necessary. Conversely, parameters that lack predictive value for the presence of ILD changes on HRCT scan may be omitted from the clinical screening protocol.

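### The primary objective is diagnostic value, but the stated primary analysis tests group differences, uses p < 0.20 to call a parameter diagnostic, and names no accuracy measure or decision threshold

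*Protocol article*

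**What the plan says.** Section 2.1 of the protocol article states the aim: "The primary objective of the FLORIS study is to determine the diagnostic value of parameters for early disease detection". The reference standard is the presence or absence of ILD changes on the baseline HRCT, which "will be used to determine the predictive value for early disease of a set of clinical and exploratory parameters".

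Section 2.13 says how this objective is to be tested: chi-square or Fisher's exact test for categorical variables and the t-test or Mann–Whitney test for continuous ones. It adds: "Univariate logistic regression will be used to test which parameters differ between the groups". Parameters with univariate p < 0.20 are described as diagnostic and enter a multivariable logistic regression with backward elimination, which is to identify the strongest predictors. If too many qualify, the cut-off becomes p < 0.10.

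The Discussion names two hoped-for uses. One is triage, "making it possible to select who should undergo an HRCT scan and for whom this is not (yet) necessary". The other is pruning: "parameters that lack predictive value for the presence of ILD changes on HRCT scan may be omitted from the clinical screening protocol".

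The only sensitivity and specificity in the article belong to an external study of digital auscultation in patients with rheumatoid arthritis (section 2.5).

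**The concern.** Whether two groups differ and whether a parameter tells individuals apart are different questions. A p-value mixes the size of the separation with the sample size, and it says nothing about how many affected relatives a rule would miss or how many unaffected relatives it would spare a scan. Calling a parameter diagnostic because p < 0.20 treats a lenient entry filter as if it measured accuracy.

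Two errors could follow. A marker barely better than chance could be reported as having diagnostic value. A useful marker could be dropped from clinical screening because it missed a p-value cut-off in a study with about 37 cases. In addition, if no threshold or operating point is fixed beforehand, any accuracy figures reported later would rest on choices made after seeing the data.

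**Working it through.** **Inputs.** Section 2.12 gives N = 200, a pilot yield of 13/73, a literature range of 16–23%, and an expected split of 37 with and 163 without ILD changes. The article gives no effect size, so the standardized mean differences (SMD, d) below are assumptions and are shown as a range. The model is a single normally distributed marker with equal variance in both groups.

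**The plan's own figure.** 200 × 13/73 = 35.6, and the literature range gives 32 to 46. The stated 37 (18.5%) is consistent with both.

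**Formulas.**
- Test statistic: d × √(37 × 163/200) = d × 5.491.
- AUC = Φ(d/√2).
- Specificity at 90% sensitivity = Φ(d − 1.2816).
- NPV at 90% sensitivity = 163 × specificity / (163 × specificity + 3.7), where 3.7 is 10% of 37 cases.

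**Smallest difference that reaches each p-value cut-off** (normal approximation):

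| p | d | AUC | Specificity at 90% sensitivity |
|---|---|---|---|
| 0.20 | 1.2816/5.491 = 0.23 | 0.57 | 15% |
| 0.10 | 1.645/5.491 = 0.30 | 0.58 | 16% |
| 0.05 | 1.960/5.491 = 0.36 | 0.60 | 18% |

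**Larger differences:**

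| d | p | AUC | Specificity at 90% sensitivity | NPV |
|---|---|---|---|---|
| 0.50 | 0.007 | 0.64 | 22% | 0.91 |
| 1.0 | < 0.001 | 0.76 | 39% | 0.94 |
| 1.5 | < 0.001 | 0.86 | 59% | 0.96 |

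For d = 0.50 in full: 0.50 × 5.491 = 2.75, so p = 0.0066 on 198 degrees of freedom. Specificity = Φ(−0.78) = 0.217, and 0.217 × 163 = 35.4 unaffected relatives fall below the cut-off, with 3.7 of the 37 cases missed. NPV = 35.4/(35.4 + 3.7) = 0.905. With no test at all it is 163/200 = 0.815.

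**The reverse direction.** An observed AUC of 0.60, at the edge of p = 0.05, has a Hanley–McNeil standard error of 0.0535 with 37 and 163 participants, so its 95% interval runs from 0.49 to 0.70. At the edge of p = 0.20 (AUC 0.566, standard error 0.0536) the interval is 0.46 to 0.67. Missing either cut-off is therefore compatible with a marker of modest real value.

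**Precision of accuracy estimates at this size.** An observed sensitivity of 33/37 (0.89) has a 95% Wilson interval of 0.75 to 0.96. An observed AUC of 0.80 has an interval of 0.71 to 0.89. The estimates are usable but not tight.

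**The case against.** The strongest reply is that the planned analysis already contains most of what is needed. Logistic regression gives odds ratios and predicted probabilities. The percentage with crackles among those with ILD changes is a sensitivity, and the percentage without crackles in the other group is a specificity. The Mann–Whitney statistic divided by 37 × 163 is an AUC. This stands. A reader might infer that the plan yields nothing but p-values or cannot answer its primary question; the article does not support that. What remains is that none of these quantities is named as a result and no operating point is set.

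It can also be said that p < 0.20 is only an entry filter. That is how it functions, but the text still attaches the word diagnostic to it.

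The triage use is introduced as an ideal in the Discussion and is not an endpoint, so failure to deliver it cannot be charged as a broken commitment. The mismatch with section 2.1 does not depend on it.

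A reader might further infer from section 2.4 ("ILD changes are defined as extensive disease, familial interstitial lung abnormalities (FILA) or minimal FILA") that extensive cases will drive the contrast. No document gives the mix of grades, so this is a possibility without a figure behind it.

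The d = 0.50 illustration is one assumed scenario for one marker. Stronger markers do better, as the table shows, and the stated hypothesis concerns a combination of markers.

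Finally, this is a condensed article, and a fuller document may name accuracy measures. The point still holds because section 2.13 does commit to a primary analysis, and that analysis does not match the objective.

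**Conclusion.** The concern holds in a limited form. The stated primary analysis consists of difference tests and p-value-driven selection, whereas the objective is diagnostic value. No accuracy measure or decision threshold is named, although the planned data and model could produce them.

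Under a single equal-variance normal marker and the expected 37/163 split, a parameter can be labelled diagnostic at an AUC of about 0.57, and can reach p = 0.05 at about 0.60. Even p = 0.007 corresponds to AUC 0.64 and 22% specificity at 90% sensitivity. These figures depend on the assumed distribution and SMD; at SMD 1.0 they would be 0.76 and 39%. Significance does not establish diagnostic value here, and non-significance does not justify omitting a parameter for lack of predictive value.

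**What to change.** In section 2.13, make accuracy estimates with 95% confidence intervals the primary analysis:

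- AUC for each continuous parameter and for the final model.
- Sensitivity, specificity, PPV and NPV for binary signs (crackles, clubbing) and for the final model, with the model's specificity and NPV read at a sensitivity fixed before the data are analysed.
- Optimism correction of the final model by bootstrapping the whole selection procedure, including the univariate screen. Backward selection on about 37 cases will otherwise inflate the apparent AUC.
- P-values kept as descriptive, and p < 0.20 no longer used to define a parameter as diagnostic. Any decision to omit a parameter should rest on its accuracy estimate and interval.
- Optionally, sensitivity by HRCT category (minimal FILA, FILA, extensive disease), reported descriptively with a warning about imprecision. If a category held 10 cases (an assumption), 9/10 detected would have a 95% Wilson interval of 0.60 to 0.98.

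The cost is revised analysis wording and a few extra outputs from data already being collected. Reported precision will look less favourable than a list of p-values, as the interval for 33/37 shows.

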### 2.10. Six-Minute Walk Test

The six-minute walk test (6MWT) is used in patients with chronic respiratory disease, with the test being primarily a test of physical capacity [53,54]. Walking distance, heart rate and O2 saturation (sat), together with subject length, weight, Borg Dyspnea and Leg Fatigue scales (1–10), will be noted according to standard protocol. Previous studies showed a shorter six-minute walk distance is present in patients with an increased risk of mortality for patients with IPF, chronic obstructive pulmonary disease, ILD, pulmonary hypertension and those awaiting transplantation [53,55]. Interestingly, among a group of IPF patients with relatively mild disease (defined as FVC% predicted ≥ 80%), oxygen desaturation during the 6-MWT was the only significant predictor of death or progression within 12 months [56]. Little is known about the value of the 6MWT in earlier stages of the disease. However, the 6MWT is a validated test that can be easily performed outside of the hospital and requires few resources, making it a potential cost-effective screening tool.

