By performing a prospective study into the prognostic value of screening parameters in the target population and the appropriate clinical setting, the FLORIS study aims to further develop an evidence-based screening protocol for first-degree relatives of FPF patients. There will be an emphasis on easily operable parameters.

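### The single pooled backward model does not directly show how well a combination of easy-to-use markers predicts ILD changes, which the Discussion emphasises

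*Protocol article*

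**What the plan says.** Section 2.13 gives one multivariable route for the primary objective. Each parameter first has a group comparison and a univariate logistic regression. Those with p < 0.20 (p < 0.10 if too many qualify) "will subsequently be assessed in a multivariate logistic regression analysis using the backward method to determine which are the strongest predictors" of ILD changes at baseline. The parameters listed there are FVC, TLC, DLCO, cough VAS, MMP7, CCL18, KL-6, SP-D, five walk-test measures, crackles, clubbing, MRC dyspnoea and MUC5B genotype. They are not divided by setting or ease of use, and no model restricted to simple markers is described. Section 2.1 likewise treats clinical and exploratory parameters as one set.

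The Discussion (Section 3) hypothesises that symptoms and physiological markers can predict disease in combination. It then looks ahead to a possible move of screening into general practice: "There will be an emphasis on easy-to-use, minimally invasive markers to investigate whether (a subset of) the screening activities could be transferred to the general" (the quote stops one word short of naming that setting). Its closing paragraph repeats: "There will be an emphasis on easily operable parameters". Section 2.10 supports the walk test on the ground that "the 6MWT is a validated test that can be easily performed outside of the hospital and requires few resources". Section 2.6 measures TLC in the body box.

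Section 2.12 gives the size: "we will include 200 participants, with an expected ratio of 37 participants with the presence of ILD changes and 163 participants with the absence".

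**The concern.** Backward elimination judges each marker conditional on everything else still in the model. A cough score or crackles finding is kept only if it adds information once DLCO, TLC, MMP7 and the rest are known. Where those tests are not available, the useful quantity is what the simple markers achieve together without them. The pooled model estimates that only if it happens to finish with simple markers alone. The univariate analyses do not supply it either, because they take one marker at a time.

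At stake is the reading of the result. The Discussion says that parameters without predictive value for ILD changes may be dropped from clinical screening. If elimination from the pooled model were read as lack of predictive value, a marker could be set aside only because it overlaps with a test that another setting would not have. Conversely, any statement about general practice would have no accuracy estimate behind it.

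**Working it through.** **The plan's own figure.** The pilot is 13/73 = 17.8%, so 200 × 13/73 = 35.6 expected participants with ILD changes (36 with the rounded 18%). The literature range in Section 2.12, 16–23%, gives 32 to 46. The stated 37 (37/200 = 18.5%) is consistent with both and is used below.

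**Would simple markers reach the pooled model?** For an assumed difference of 0.5 SD, the standardised effect is 0.5 × √(37 × 163/200) = 2.75. Power is Φ(2.75 − 1.96) ≈ 78% at two-sided 0.05, and the chance of passing p < 0.20 is Φ(2.75 − 1.28) ≈ 93%. Moderately useful simple markers would usually enter.

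**What happens to them there?** Assume normal markers with a common within-group correlation ρ: three specialised and three easy-to-use. With p markers whose SD differences are μ and sum to S, the population logistic coefficient of marker j is

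b_j = [μ_j − ρS / (1 + (p − 1)ρ)] / (1 − ρ).

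With differences of 0.8 (specialised) and 0.5 (easy), p = 6 and S = 3.9. For an easy marker:
- ρ = 0.3: (0.5 − 0.468)/0.7 = 0.05
- ρ = 0.5: (0.5 − 0.557)/0.5 = −0.11
- ρ = 0.7: (0.5 − 0.607)/0.3 = −0.36

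The same marker alone has coefficient 0.5. At ρ = 0.7 an easy marker may survive, but with an expected sign opposite to its own association. Survival there says little about its usefulness alone.

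The AUC of the easy set is Φ(D/√2), with D² = k d²/(1 + (k − 1)ρ) for k markers of difference d. For k = 3, d = 0.5 and ρ = 0.5, D² = 0.75/2 = 0.375 and AUC = Φ(0.433) = 0.67.

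**Simulation** (37 v 163; p < 0.20 screen; backward removal at p > 0.05, an assumed level; 400 runs per row):

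| ρ | SD difference, specialised / easy | Final model has no easy marker | Final model has easy markers only | AUC, easy set | AUC, all six |
|---|---|---|---|---|---|
| 0.3 | 0.8 / 0.5 | 75% | 0% | 0.69 | 0.78 |
| 0.5 | 0.8 / 0.5 | 84% | 1% | 0.67 | 0.76 |
| 0.7 | 0.8 / 0.5 | 52% | 1% | 0.65 | 0.76 |
| 0.3 | 0.6 / 0.6 | 20% | 19% | 0.72 | 0.74 |
| 0.5 | 0.6 / 0.6 | 38% | 41% | 0.70 | 0.71 |
| 0.7 | 0.6 / 0.6 | 47% | 50% | 0.68 | 0.69 |

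In the first three rows, backward selection among the easy markers alone kept at least one in 97%, 93% and 89% of runs.

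A second layout used two easy markers (0.6 SD) and three specialised ones (0.8 SD), with removal at p > 0.10 or p > 0.05. Both easy markers were dropped in about 76–85% of runs at ρ = 0.5 and 53–65% at ρ = 0.3, although their joint AUC is 0.69 and 0.70. With equal differences of 0.5 SD the figure was 33–56%.

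**Room for parameters.** Section 2.13 names 4 categorical and 8 continuous parameters plus 5 walk-test measures, 17 in all: 37/17 = 2.2 events each if all entered. An eight-item easy-to-use set would have 37/8 = 4.6; a set of four or five has 37/4 = 9.3 or 37/5 = 7.4.

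**The case against.** The strongest reply is that Section 2.13 does what the formal objective asks. Section 2.1 wants the diagnostic value of a set of clinical and exploratory parameters, and a model seeking the strongest predictors serves that. General practice appears only in the Discussion, as an emphasis for the future. Selection of relatives for HRCT is a separate hope there, with no setting named. The hypothesis is also framed as prediction beyond methods now in use, and for that added-value question a model containing lung function is suitable. All of this stands, so the point is a mismatch with a declared emphasis and not a failure of the primary analysis.

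Three stronger readings are tempting but unsupported:
- A reader might infer that the plan cannot answer the general-practice question at all. The univariate analyses still report each simple marker, and the pooled model may end with simple markers only.
- A reader might infer that general practice is the target setting. The documents do not say so.
- A reader might infer that the plan will discard the simple tools it wants to promote. The Discussion speaks of parameters lacking predictive value and does not equate that with elimination from the model.

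The split into easy-to-use and specialised tests is also a judgement. The text supports it for the walk test and suggests it for body-box TLC, but gives no classification. The simulated effects and correlations come from no document, and crackles and clubbing are binary but were simulated as normal. Finally, the article is condensed, and a restricted model may exist in a fuller document; confirming it would settle the point. What survives is that the described method is a stated choice, and it leaves the emphasised combination unestimated.

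**Conclusion.** The concern holds in limited form. The pooled backward model fits the formal aim but does not directly show whether a combination of easy-to-use markers predicts ILD changes well enough to support moving part of screening to general practice. That conclusion follows from how conditional selection works and needs no simulation.

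Its size is uncertain. With two easy markers, both were eliminated in about 33–85% of runs. With three easy markers, all were eliminated in 52–84% when the specialised tests were stronger and in 20–47% when effects were equal. These figures rest on assumed effect sizes, a common correlation, normal markers and assumed removal thresholds. They show that elimination is compatible with a useful simple set (AUC 0.65–0.72 in the table), not how often it will occur in this study. This is an inexpensive improvement to the analysis, not an error in the primary objective.

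**What to change.** In Section 2.13, keep the pooled model for the strongest-predictor aim and add the following:

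1. Name in advance a short easy-to-use set that about 37 events can carry, for example age plus a few of crackles, MRC dyspnoea, cough VAS and one walk-test measure. The study team should decide which tests count as easy to use.
2. Fit that set as specified, without univariate screening or backward elimination, and report its AUC, sensitivity and specificity against the baseline HRCT with confidence intervals.
3. Report the gain from adding lung function, and then from adding biomarkers and genotype.
4. Base any general-practice statement on the easy-to-use set, and state that elimination from the pooled model is not evidence of lacking predictive value.

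No new data are needed. The cost is analysis wording and one or two more reported models; fixing the sets in advance limits the added multiplicity. Precision will be modest: an assumed sensitivity of 0.80 in 37 participants has standard error √(0.8 × 0.2/37) = 0.066, so a 95% interval of roughly 0.67 to 0.93.
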